### Cognitive behavioural therapy intervention

The cognitive behavioural therapy modules developed for the study will be simple, easy, and understandable such that the intervention can be given even by even a lay person. The behavioural therapy intervention will consist of individual sessions of 30–45 minutes duration, that will be delivered by a trained nurse. The sessions will be given in the outpatient settings of the study sites. We will use a detailed trainer’s manual to explain the sessions to the research nurse. The delivery of the brief behavioural counselling sessions will be based on a structured guidance document. Participants will receive individual face-to-face sessions once a month and telephone sessions once a week for the next 10 months. The cognitive behavioural therapy sessions will generally involve building rapport with patients, understanding patient’s thoughts and belief about HF, assessing their dysfunctional thoughts, teaching them methods to cope with the disease, incorporating positive thoughts, teaching them methods to relax the mind and reviewing the assignments given to each individual patient. At the end of each session, participants will be required to complete the ‘Mood thermometer
^
26
^’ to see how they feel each day and their mood changes throughout the therapy.

All participants receiving the cognitive behavioural therapy interventions will be given a behavioural therapy manual in their native language. This self-help manual will aid in guiding the participants in unsupervised home tasks and assignments based on behavioural therapy. A self-assessment checklist (
*Extended data*)
^
27
^ will be provided and it will help the participants in monitoring their progress and in attaining therapy-related goals during the follow-up periods.

### Outcome measures

Time to mortality will be the primary outcome for the proposed study. A composite outcome of mortality and hospitalisation for HF will be considered as the main secondary outcome. Additional secondary outcome variables will include ‘days alive and out of hospital (DAOH)’, cumulative hospitalisation rate, disease-specific and general quality of life, depression score, six minutes walking distance, handgrip strength, and adherence to medicines and lifestyle.

### Measurements

The socio-demographic details like age, gender, education, occupation will be recording during the patients’ first visit. Aetiology, history and risk factors for the disease will also be recorded at baseline. Furthermore, recent blood investigations done in the three months prior will be also analysed.

Participants will be seen every three months until the end of the three-year follow-up
^
28
^ will help to identify measurement details at different time points. At study visits, depression and anxiety scores will be collected from each participant by using the PHQ9
^
29
^ and GAD-7
^
30
^ questionnaires, respectively. The self- management component will include assessments of participant’s medication adherence, management of weight and diet, and family support as reported by the patient. The medication adherence will be measured using the four-item Morisky Green Levine medication adherence scale
^
31
^. We will use the multimorbidity treatment burden questionnaire (MTBQ)
^
32
^, to measure treatment burden. The study proforma will also assess the medical utilisation, patient satisfaction in quality of care, family support, and diet management.

We will use the Kansas City Cardiomyopathy Questionnaire (KCCQ)
^
33
^ and EQ-5D-5L
^
34
^ to assess quality of life. The KCCQ assess the disease specific quality of life. The EQ-5D-5L provides a simple descriptive profile and a single index value for health status. Standardized and validated instruments will be used for assessing the functional status, severity of disease, and treatment.

The six-minute walk test (6MWT) will be measured using standard settings during their out-patient visits
^
35
^. The 6MWT will be performed indoors, on a flat-surface corridor, which is 30 m long. Before starting the test, the research nurse will record the blood pressure, pulse rate, and oxygen saturation. The patient will be advised to start the test after being instructed on the test procedure. The test will run for six minutes and will follow all the instructions given by the American Thoracic Society
^
36
^. At the end of the test, the distance covered will be documented along with the pulse rate, blood pressure, oxygen saturation and Borg’s rating of perceived exertion and fatigue.

Hand grip strength will be assessed using standard assessment procedures using a dynamometer
^
37
^. In brief, hand dominance will be determined, following which the test will be carried out with the patient in a sitting position. The arm will be supported and positioned at right angles with the elbow. The forearm will be in the mid-prone position. The participant will be asked to make a tight fist without moving the wrist or the elbow while squeezing the dynamometer, which should be maintained for at least five seconds. Care will be taken to avoid Valsalva manoeuvres during this time. The average of the three attempts with a resting period of 15 seconds between attempts will be performed and the best value among them will also be recorded during the procedure
^
38
^.

### Sample size

Assuming a three-year cumulative event rate of 50% or more for the primary outcome (mortality)
^
39
^, it was estimated that a sample size of 1632 participants would provide 80% power to detect at least 20% relative risk reduction of the primary outcomes for each of the randomised comparisons.

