## Introduction

Heart failure (HF) is a multi-morbid chronic condition, which adversely impacts the quality of life of the affected individual
^
1,
2
^. The disease burden attributable to HF in India is increasing and the estimated prevalence ranges from 1.3 million to 4.6 million, with an annual incidence of 0.5–1.8 million
^
3
^. Heart failure requires resource-intensive treatment strategies, which are not immediately available and accessible for most patients in India. The financial burden of HF to the patients and their care givers is huge, and represents 2–3% of the total cost of all medical conditions
^
4
^. The estimated cost of HF treatment, resulting from frequent hospital admissions, multiple-drug therapy, comorbidities and device treatments
^
4
^ in 2012, is approximately $1186 million in India
^
4
^. The HF mortality in India is even worse than common cancers with an estimated 40% surviving past five years
^
5
^.

Besides the resource-intensive medical and medical device therapies, engaging the patient and their caregivers in self-care is known to reduce mortality, rehospitalisation and improve quality of life among HF patients
^
6,
7
^. In general, HF patients need to engage in a number of self-care behaviours like adherence to multiple medications, living a healthy life style (
*e.g.* no smoking or drinking alcohol), monitoring symptoms, identifying and addressing warning signs or symptoms, managing depression or psycho-social distress and other co-morbidities
^
1,
8
^. The ability to participate in and adhere to self-care behaviours becomes more challenging to people as HF symptoms worsen. Decline in physical function and increased psycho-social distress-related symptoms are common in HF patients as the disease worsens
^
8–
10
^. It may further hinder the individual’s capacity for performing self-care and deteriorates the patient condition in a vicious cycle
^
11
^.

Physical activity is an important core component of cardiac rehabilitation (CR)
^
12
^. Timely introduction of structured and graded physical activity based on the severity of HF symptoms is an important component of cardiac rehabilitation (CR) and is associated with improvements in functional capacity, and quality of life
^
13
^. Studies focusing on CR in India are limited. Even though preliminary works suggesting the benefits of exercise-based CR on functional capacity and quality of life exist
^
14

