### Study design

We will conduct a 2×2 factorial, randomised, and open label trial to evaluate the specific effects of physical activity and behavioural therapy in reducing mortality and hospitalisation in HF patients in India. The patients recruited in the study will be randomly assigned to one of four intervention groups: a control arm (usual care-C), intervention A (physical activity), intervention B (cognitive behaviour therapy), and a combination of intervention A and B (physical activity + cognitive behaviour therapy)
^
19
^. We assumed no interaction between the treatment arms. 

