### Randomisation and blinding 

Treatment allocation at each site will be assigned using an automated randomization process developed by an independent person who is not involved in the study. Computer-generated random numbers will be used for randomisation into four groups. Units of randomisation will be HF patients attending the outpatient department of the selected hospitals. Consenting participants will be allocated to one of the four groups (three intervention groups or one usual care group) in a 1:1:1:1 ratio using a central randomisation system. Randomisation will be stratified by site. The randomisation listing will be attached to the
REDCap system for automatic online randomization upon completion of screening and collection of all baseline data. The trial is open-label, and patients and investigators will be aware of treatment allocation.

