### Statistical analysis

Baseline characteristics and follow-up measurements will be described using descriptive summary measures depending on the level and scale of measurements. Intention to treat analyses will be performed. The effects of intervention on the primary mortality endpoints will be estimated from unadjusted Cox proportional hazard models. We will combine mortality and hospitalisation for HF as a composite secondary outcome. To analyse the composite outcome, in participants with more than one outcome event during follow-up, survival time to the first relevant endpoint will be used in the analysis. As a general practice, all participants will be censored at their date of death or, for those still alive at the end of follow-up, or at the date of their last visit. Patients with an unknown vital status will be also right censored when they were last known to be alive. To calculate the relative risk reductions, we will use the formula based on the hazard ratio ([1–hazard ratio] ×100). The reciprocals of the absolute risk differences with their normally approximated 95% confidence intervals (CIs) will be calculated as the numbers needed to treat. For the continuous secondary outcomes variables, differences between randomised groups during follow-up will be estimated from linear mixed models or generalised estimating equations (GEE) as appropriate. In general, all p values will be calculated from two-tailed tests of statistical significance with a Type I error rate of 5%.

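### The stated 80% power at 1632 patients matches an arm-against-arm comparison of proportions, not the factorial main effects under the planned Cox analysis

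*Protocol article*

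**What the plan says.** Four parts of the protocol article bear on the point.

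- **Sample size.** The control rate is given as "Assuming a three-year cumulative event rate of 50% or more for the primary outcome (mortality"). The claim is that "a sample size of 1632 participants would provide 80% power to detect at least 20% relative risk reduction", and it is made "for each of the randomised comparisons". No formula, effect scale or loss allowance is given, and the comparisons are not named.
- **Study design.** The trial is a 2×2 factorial aimed at the separate effect of each intervention: "We assumed no interaction between the treatment arms". The Conclusions likewise speak of each component working independently.
- **Randomisation and blinding.** "Consenting participants will be allocated to one of the four groups (three intervention groups or one usual care group) in a 1:1:1:1 ratio". With 1632 patients that is 408 per cell, or 816 vs 816 when each factor is compared at its margins.
- **Statistical analysis.** Mortality is analysed by an unadjusted Cox model, and relative risk reduction is computed as (1 − hazard ratio) × 100. In general "all p values will be calculated from two-tailed tests of statistical significance with a Type I error rate of 5" per cent. The text does not say whether cells are pooled.

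**The concern.** Assuming no interaction has one use in a 2×2 design: it lets each factor be tested on all patients, with the cells of the other factor pooled. A trial sized on that basis would quote the power of 816 vs 816. The total of 1632 looks instead like four times a two-arm sample size, which makes no use of the factorial structure. It also looks like a calculation on risks, whereas the analysis section defines the effect as a hazard ratio.

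What is at stake is how the result is read. One statistician could follow the text and test two pooled main effects. Another could test each active arm against usual care. Both could cite the same 80%, yet the two analyses differ widely in power. The trial is open-label, so the primary contrast should be fixed before outcome data are seen by arm.

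**Working it through.** **Inputs.** N = 1632, power 80%, control three-year mortality 50% (the stated minimum) and relative reduction 20% come from Sample size. Two-sided 5% comes from Statistical analysis, and 1:1:1:1 allocation from Randomisation and blinding. The normal quantiles are 1.960 and 0.842.

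**1. Reproducing 1632.** Read as risks, a 20% reduction is 50% vs 40%, with mean 45%.

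- Pooled two-proportion formula: n = [1.960·√(2·0.45·0.55) + 0.842·√(0.50·0.50 + 0.40·0.60)]² / 0.10² = 387.3, so 388 per group.
- Continuity correction: n′ = (n/4)·[1 + √(1 + 4/(n·0.10))]² = 407.1, so 408 per group.
- 4 × 408 = 1632, an exact match.
- Near misses: 4 × 388 = 1552 without the correction, and 1540 with unpooled variance. Inflating 1552 by an assumed 5% gives 1630 to 1634, but that is also an arm-against-arm basis.

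**2. Power on the risk scale.**

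| Contrast | Risks | Power, uncorrected | Power, continuity-corrected |
|---|---|---|---|
| 408 vs 408 | 50% vs 40% | 82.0% | 80.1% |
| 816 vs 816, other factor inert | 50% vs 40% | 98.3% | 98.0% |
| 816 vs 816, other factor also effective | 45% vs 36% | 96.0% | 95.5% |

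In the last row the control margin averages 50% and 40%, and the treated margin averages 40% and 32%.

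**3. Power on the planned scale.** Under the protocol's own definition, a 20% reduction is a hazard ratio (HR) of 0.80. Schoenfeld's formula with equal allocation gives the deaths needed for 80% power: D = 4·(1.960 + 0.842)² / (ln 0.80)² = 4 × 7.849 / 0.04979 = 630.5, so 631.

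Expected deaths assume proportional hazards, three years of follow-up for everyone and no loss. Three-year mortality is 50% under usual care, 1 − 0.5^0.80 = 42.57% with one effective intervention, and 1 − 0.5^0.64 = 35.83% with two. Power = Φ(½·√D·|ln 0.80| − 1.960).

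| Contrast | Expected deaths | Power |
|---|---|---|
| Margin, other factor inert | 816 × (0.50 + 0.4257) ≈ 755 | 86.6% |
| Margin, both factors effective | 408 × (0.50 + 2 × 0.4257 + 0.3583) ≈ 698 | 83.8% |
| One arm vs usual care | 408 × (0.50 + 0.4257) ≈ 378 | about 58% |

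**4. Effect of losing deaths (assumed rates; the protocol gives none).** With both factors effective, losing 10% leaves about 628 deaths and 79.8% power. With the other factor inert, losing 15% leaves about 642 deaths and 80.7% power.

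**5. Why the two scales differ.** A fall from 50% to 40% corresponds to a hazard ratio of ln 0.60 / ln 0.50 = 0.737, a larger effect than 0.80. Figures in step 2 must not be compared with those in step 3 as if they described the same effect.

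**The case against.** The best defence has three parts.

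First, the protocol nowhere says that the sizing was pairwise. That is right, and the basis remains an inference. It is a strong one, because the match is exact and needs only the stated inputs and a standard formula.

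Second, on the hazard scale the main effects have 84% to 87% power before loss, so a modest unstated loss allowance would make 80% a fair description. This also stands as a statement about the likely operating power. It does not explain 1632. For example, 1475 patients for 80% with both factors effective, allowing for 10% loss, gives 1475 / 0.90 ≈ 1639, close but not equal and resting on a loss rate that the document does not contain.

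Third, if the comparisons are each arm against usual care, 80% is correct on the risk scale. That holds for a two-proportion test. It does not hold for the planned Cox analysis with HR 0.80, where the power is about 58%, and it leaves the no-interaction assumption with no role.

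The choice of contrasts could also be made in an analysis plan that is not shown, and its absence is not the point here. The protocol itself fixes a design, an effect definition and a power figure that do not fit together.

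Some stronger readings are tempting and should be resisted.

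- A reader might infer that the trial is too small. For the main effects it is not, on either scale.
- A reader might infer that it is about twice the size needed, since 80% at the margins on the risk scale takes 776 to 976 patients. That rests on a test of proportions that the protocol does not plan.
- If the combination adds nothing beyond either intervention alone, the marginal HR is √0.80 ≈ 0.89 and power is about 32%. That contradicts a declared assumption and is a sensitivity scenario.
- The Introduction's five-year figure, "with an estimated 40% surviving past five years", implies 1 − 0.40^(3/5) = 42% three-year mortality, but only under a constant hazard that the protocol does not assert. The 50% has its own citation, which is not available here, so no error is shown.

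**Conclusion.** The point stands at moderate severity. The 80% attached to 1632 patients coincides with a continuity-corrected risk comparison of one arm with another. Under the planned analysis it describes neither candidate contrast: before loss, the main effects have 83.8% to 86.6% power and a single arm against usual care about 58%. On the risk scale the corresponding figures are 96% to 98% and 80% to 82%.

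The hazard-scale figures rest on 50% three-year control mortality, HR 0.80 for each effective factor, proportional hazards, no interaction, two-sided 5% and complete three-year follow-up. The discrepancy is conservative for the main effects. The practical harm is an unnamed contrast and a power claim that would mislead anyone who applied it to a single arm against usual care.

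**What to change.** Revise the Sample size paragraph, with a matching sentence under Statistical analysis.

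1. Name the two at-the-margins main effects as the primary comparisons: physical activity yes vs no, and cognitive behavioural therapy yes vs no, each 816 vs 816.
2. State the effect as a hazard ratio of 0.80 and give power in deaths: 631 for 80%; about 698 to 755 expected before loss, for about 84% to 87%. Add that power is about 80% if 10% of deaths are lost with both factors effective, or 15% with the other factor inert, and label those rates as assumptions.
3. State that comparisons of one arm with usual care are not powered at 80% for HR 0.80 (about 58%).
4. State the formula used for 1632. If the basis was different from the one inferred here, say so.

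The cost is rewording. No extra patients or data collection are needed, and the change should be made before any outcome data are examined by arm.

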### Randomisation and blinding 

Treatment allocation at each site will be assigned using an automated randomization process developed by an independent person who is not involved in the study. Computer-generated random numbers will be used for randomisation into four groups. Units of randomisation will be HF patients attending the outpatient department of the selected hospitals. Consenting participants will be allocated to one of the four groups (three intervention groups or one usual care group) in a 1:1:1:1 ratio using a central randomisation system. Randomisation will be stratified by site. The randomisation listing will be attached to the
REDCap system for automatic online randomization upon completion of screening and collection of all baseline data. The trial is open-label, and patients and investigators will be aware of treatment allocation.

### Data management

All data collected from the patients and during the telephonic follow-up with each patient will be recorded in the study proforma. The data collection will be done using the REDCap application. All the participating centres will be given dedicated login credentials to enter the data. The data will be protected for privacy with the following standard precautions: We will assign a unique identification number to all participating centres and for each enrolled patient, so that they will be further identified only by that number; individual patient identification details will be collected and maintained only at the participating centres. The data will be entered by the research nurse under the supervision of the concerned cardiologist (investigator).

All the data fields in the REDCap application will be clearly defined and appropriate validation checks will be incorporated. For ease of operation, all study staff will have access to a procedural manual of operation. To ensure data validity and to identify discrepancies in data entry, the ‘edit check programs’ in REDCap will be used. Discrepancies or inconsistent data, missing data, range checks, and deviations will be identified. The data will be downloaded from the REDCap application and a data validation process will be run frequently to identify potential errors. All discrepancies will be resolved periodically. Ongoing quality control of data will be undertaken at regular intervals during data collection. Reviewing discrepancies, investigating the reason, and resolving them with documentary proof will be initiated in the data validation process.

The final data validation will be run after a proper quality check and assurance. If there are no issues, the datasets will be finalized in consultation with the study statistician. All data management activities will be completed prior to database lock. To ensure this, a pre-lock checklist will be used, and completion of all activities will be confirmed. Once the approval for locking is obtained from all investigators, the database will be locked, and the final data set will be extracted for statistical analysis.

A data management plan (DMP) will be created to understand who is responsible for creation, storage, and maintenance of the data and maintaining the privacy of the data collected. As per the DMP the authorized authority to view data will be the principal investigator and any other person as authorized by the principal investigator. The data will be saved in the inhouse server of SCTIMST.

### Statistical analysis

Baseline characteristics and follow-up measurements will be described using descriptive summary measures depending on the level and scale of measurements. Intention to treat analyses will be performed. The effects of intervention on the primary mortality endpoints will be estimated from unadjusted Cox proportional hazard models. We will combine mortality and hospitalisation for HF as a composite secondary outcome. To analyse the composite outcome, in participants with more than one outcome event during follow-up, survival time to the first relevant endpoint will be used in the analysis. As a general practice, all participants will be censored at their date of death or, for those still alive at the end of follow-up, or at the date of their last visit. Patients with an unknown vital status will be also right censored when they were last known to be alive. To calculate the relative risk reductions, we will use the formula based on the hazard ratio ([1–hazard ratio] ×100). The reciprocals of the absolute risk differences with their normally approximated 95% confidence intervals (CIs) will be calculated as the numbers needed to treat. For the continuous secondary outcomes variables, differences between randomised groups during follow-up will be estimated from linear mixed models or generalised estimating equations (GEE) as appropriate. In general, all p values will be calculated from two-tailed tests of statistical significance with a Type I error rate of 5%.

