### Study settings

The study will be carried out in six hospital settings with facilities for management of HF in Kerala, India. Medium to large tertiary care referral hospitals in both private and public settings will be selected for the study with representation from the Southern, Central and Northern parts of Kerala, India.

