### Study population

Eligible patients with physician-diagnosed HF
^
2
^ will be invited from the selected hospitals for participation in the trial. HF patients with New York Heart Association (NYHA) class I to IV will be invited to participate in the study. Adults over 18 years old, citizens of India, permanent residents of the state of Kerala, who speak Malayalam language and with physician-diagnosed HF will be included in the trial. We will exclude bedridden patients, patients with known psychiatric disorders and under treatment, and those who refuse to provide written informed consent from the trial. Further, we will exclude currently enrolled patients in other formal cardiac rehabilitation programs.

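### The primary Cox model is stated as unadjusted although randomisation is stratified by site; if sites differ in mortality, the test is conservative and loses some power

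*Protocol article*

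**What the plan says.** All of this is in the protocol article.

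- Statistical analysis, on the primary outcome: "The effects of intervention on the primary mortality endpoints will be estimated from unadjusted Cox proportional hazard models". Tests are two-sided at 5%, and the relative risk reduction is defined as one minus the hazard ratio. The section mentions neither site nor how the two randomised factors enter the model.
- Randomisation and blinding: "Randomisation will be stratified by site". No other stratification factor is named. Allocation to the four groups is "in a 1:1:1:1 ratio using a central randomisation system".
- Study settings: "The study will be carried out in six hospital settings". They are public and private and lie in different parts of Kerala.
- Study design: "We will conduct a 2×2 factorial, randomised, and open label trial", and "We assumed no interaction between the treatment arms".
- Study population: "HF patients with New York Heart Association (NYHA) class I to IV will be invited to participate in the study".

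The article gives no reason for leaving site out, no site-stratified or adjusted sensitivity analysis, and no figure for how much mortality varies between hospitals.

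**The concern.** Stratified randomisation forces the arms to be balanced within each hospital. That removes one source of chance difference between arms, namely different shares of patients from high- and low-mortality hospitals. An analysis that ignores site does not credit this, so its model-based standard error is too large whenever hospitals differ in mortality. In a Cox model, leaving out a prognostic variable also moves the hazard ratio towards 1. Both effects make a real mortality effect harder to detect. Six public and private referral hospitals in different regions may well differ in mortality, so the question is how much this costs.

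**Working it through.** **The plan's own figure.** Sample size section: three-year mortality 50%, 20% relative reduction (so 50% against 40%), 80% power; two-sided 5% from Statistical analysis.

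- Two proportions: n = [1.960 × √(2 × 0.45 × 0.55) + 0.842 × √(0.50 × 0.50 + 0.40 × 0.60)]² / 0.10² = 387.3, so 388 per arm.
- With continuity correction: (388/4) × [1 + √(1 + 4/(388 × 0.10))]² = 407.8, so 408 per arm.
- 4 × 408 = 1632, the stated total. It is right under its own inputs and does not depend on site.

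**Power of the main-effect comparison at a hazard ratio of 0.80.** I take the factorial comparison at the margins, 816 against 816, with the other factor inactive.

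- Three-year mortality under treatment: 1 − 0.50^0.80 = 0.4257.
- Deaths: 816 × (0.50 + 0.4257) ≈ 755.
- Power: Φ(|ln 0.80| × √755 / 2 − 1.960) = Φ(1.106) = 86.6%.

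**What ignoring site costs.** A simulation used 1632 patients, six equal sites, 1:1:1:1 allocation balanced within site, exponential survival, three years of follow-up, control mortality of 50% averaged over sites, no dropout, 5,000 replicates per scenario and a Wald test on one factor (A). The between-site standard deviation (SD) of the log hazard is an assumption, shown at 0, 0.3 and 0.6. A site one SD above average then has a hazard e^0.3 = 1.35 or e^0.6 = 1.82 times the average.

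Power for factor A at a hazard ratio of 0.80:

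| Other factor | Site SD | Unadjusted | Stratified by site, both factors | Loss (points) |
|---|---|---|---|---|
| No effect | 0 | 86.7% | 86.7% | 0.0 |
| No effect | 0.3 | 85.1% | 86.6% | 1.5 |
| No effect | 0.6 | 81.7% | 87.0% | 5.3 |
| HR 0.80 | 0 | 83.6% | 83.6% | 0.0 |
| HR 0.80 | 0.3 | 82.7% | 84.2% | 1.5 |
| HR 0.80 | 0.6 | 79.0% | 84.5% | 5.5 |

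The first row agrees with the closed form (86.7% against 86.6%). The Monte Carlo standard error is √(0.85 × 0.15 / 5000) = 0.5 points near 85% power and √(0.05 × 0.95 / 5000) = 0.3 points near 5%.

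- **Type I error** (factor A and the other factor both inactive): unadjusted 5.2%, 5.0% and 3.7% at SD 0, 0.3 and 0.6; stratified with both factors 5.1%, 5.6% and 5.7%. The fall to 3.7% is about four standard errors. The stratified values lie up to 2.3 standard errors above 5%. All scenarios used the same random seed, so these are not independent signs of inflation.
- **Mean hazard ratio** (other factor inactive): unadjusted 0.80, 0.804 and 0.816; stratified 0.80 throughout.
- **The second factor alone**: adding it to the unadjusted model changes power by at most 0.3 points (82.7% to 83.0%), which is within simulation noise, even when that factor has a hazard ratio of 0.80.

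**The case against.** The strongest reply is that an unadjusted Cox model is a legitimate choice. It targets the marginal hazard ratio, which sits naturally beside the absolute risk differences and numbers needed to treat that the article also plans. Part of the movement from 0.80 to about 0.815 is non-collapsibility, that is, a different quantity rather than a biased estimate of the same one. In the table the unadjusted test keeps 79.0% to 86.7% power against a planned 80%. The word unadjusted may mean only that no baseline covariates are used, and an analysis plan that is not shown may handle site and both factors.

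Much of this stands. The unadjusted test is not invalid, and attenuation should not be called bias. How the two factors enter the model is a detail that an article may leave to the analysis plan. The reply does not remove the mismatch over site. The article states the primary model rather than leaving it open, and on the plain reading that model excludes the stratification factor. If only baseline covariates were meant, the article should say so.

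A reader might go further in three ways that the documents do not support:

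- **That omitting the second factor gives away power.** It is balanced by design, and the loss is not measurable.
- **That the design calls for NYHA adjustment, with a large gain.** Only site is a stratification factor. With assumed hazard ratios of 1.6 or 2.0 per NYHA class, together with site variation, simulations can show power rising from 80% to 85% or from 73% to 85%. The article gives neither those effects nor the NYHA distribution, and leaving such covariates out is not an error.
- **That the power loss is certain.** If sites have equal mortality it is zero.

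**Conclusion.** The point holds as one of efficiency and calibration, and it is modest in size. The stated primary analysis does not follow the randomisation. The cost is about 0, 1.5 and 5.5 points of power at a between-site SD of the log hazard of 0, 0.3 and 0.6, with type I error falling to about 3.7% at 0.6. No false-positive risk arises, and the stated sample size is not affected.

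The mismatch itself is certain from the text. Its size is not, because it rests on between-site variation that the article does not give. It also rests on equal site sizes, close balance within site, no dropout, and the main-effect comparison at the margins.

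**What to change.** State in the protocol or analysis plan that the primary model is a Cox model stratified by site with both randomised factors as terms, each main effect being read from that model. Keep the unadjusted model as a sensitivity analysis. The second term makes clear which factorial effects are estimated; it is not there to gain power.

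Optionally, prespecify adjustment for age, which the Measurements section records at the first visit, and for baseline NYHA class if it is recorded. The article gives NYHA class only as an eligibility range, so that should be confirmed first. Such adjustment may add a few points of power, depending on how prognostic these variables prove to be.

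The cost is one sentence and no extra patients. With about 1632 / 6 = 272 patients per site if sites are equal, stratifying loses nothing when sites do not differ (86.7% power either way). The one small downside is that the hazard ratio becomes conditional on site, and on any covariates, rather than marginal. Because the trial is open-label, the change should be fixed before outcomes by arm are examined.
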